#### Participants

All patients aged 18 years or over undergoing hemodialysis treatment (thrice a week) for at least 3 months, and able to communicate in English or Malay, will be included in the study. Patients who have had any major surgical interventions in the previous three months, or have malignancies, cognitive impairment, dementia, active psychosis, or major hearing impairment, or are pregnant or breastfeeding, will be excluded.

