#### Secondary outcomes

Measuring the number of adherences, quality of life and clinical outcomes.

*a) General Medication Adherence Scale (GMAS)*. A novel GMAS will be used to measure the adherence. This scale consists of 11 questions which measure the adherence in three domains: the first 5 questions measure nonadherence due to patient behavior, followed by 4 questions measuring the comorbidity and pill burden related nonadherence, and the final 2 questions measuring cost-related nonadherence. Each question has 4 possible answers—always, mostly, sometimes, and never—which will be awarded a score of 0, 1, 2 or 3, respectively. A cumulative medication adherence score of 30 to 33 will be considered as high adherence, followed by a score of 27 to 29 as good adherence, a score of 17 to 26 as partial adherence, a score of 11 to 16 as low adherence and lastly poor adherence for patients scoring 0 to 10. This adherence tool has been validated to measure medication adherence among chronically ill patients [29].

*b) Kidney disease quality of life-36*. A validated KDQOL-36 questionnaire will be used to measure the quality of life among HD patients. KDQOL-36 is a disease-specific instrument that has been widely used to assess the HRQOL in ESRD patients. It contains a subset of the KDQOL-SF items, including the SF-12 items and 24 items to obtain three kidney disease-specific scales, which are burden of kidney disease (4 items), effects of kidney disease on daily life (8 items), and symptoms or problems (12 items). The three disease-specific subscales can be summated into the kidney disease component summary score. The SF-12 is developed using a subset of the SF-36 items. It will generate two summary scores, which are the physical component summary (PCS) and mental component summary (MCS). All these scores range from 0 to 100, with higher scores reflecting better health. In this study, the Malay version of the KDQOL-36 questionnaire will be used, as it is validated [30].

*c) Clinical outcomes*. Clinical outcomes such as blood glucose level, calcium, phosphate, hemoglobin and LDL levels will be obtained from the computer and medical records at the HD unit. These lab parameters will be measured at the baseline, 6^th^ month and the final of the study. The changes in the value of the clinical parameters will be analyzed to find if there is any significant difference after the intervention.

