This analysis is important as it acts as surrogate marker for adherence and can be corelated with GMAS scores to show that lab parameters will be within the desired range if patient adherence is improved.

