#### a) Medication review

MR is a well-structured method to optimize medication use and improve health outcomes among patients [31]. The researcher will examine patient medical records and interview patients to identify patient medication discrepancies and medication-related problems. Any medication issue related to a patient’s medicine-taking behavior and use of medicine in the context of their clinical condition will be recorded. The PCNE version 9 and kidney-related clinical practice guidelines will be used as guides. All the recorded medication problems will be discussed with relevant physician. The changes done by the physician will be notified to the researcher and can be tracked in the following follow up.

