### Study strengths & limitations

The limitation of this study is that it needs to be conducted as a pre-post study due to ethical consideration from the study site. Moreover, patients outcomes will be measured through questionnaire, recall bias and social-desirability bias may occur. Another limitation is the selection of 25% as the dropout rate for current study. As ESRD patients are high risk patients with high mortality and morbidity rates, an addition of 25% drop out rate to the total number of sample size may be an underestimation. Moreover, as the patient adherence will be measured using GMAS score, there is potential for overestimation of medication adherence and susceptibility to manipulation. However, patient clinical outcomes will be monitored to estimate an overall medication adherence rate. Nevertheless, medication adherence rate is susceptible to under or overestimation. The strength of this study is that it will be conducted in multicenter sites.

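### Laboratory values are read as a marker of adherence in all enrolled patients, although no one need be prescribed a drug for the parameter and the review itself can change prescriptions

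*Protocol article*

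**What the plan says.** The Participants section admits "All patients aged 18 years or over undergoing hemodialysis treatment (thrice a week) for at least 3 months", subject to language ability and a list of exclusions. None of these criteria concerns the drugs a patient takes. The conditions that the laboratory values relate to are neither required nor excluded.

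Under Secondary outcomes, "Clinical outcomes such as blood glucose level, calcium, phosphate, hemoglobin and LDL levels will be obtained from the computer and medical records". The article names no subset for their analysis: "The changes in the value of the clinical parameters will be analyzed to find if there is any significant difference after the intervention". (Study procedure and follow up lists glycosylated hemoglobin and a lipid profile in place of glucose and LDL.)

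The same section then gives this analysis a second role: "This analysis is important as it acts as surrogate marker for adherence and can be corelated with GMAS scores". The stated purpose is that the values "can be corelated with GMAS scores to show that lab parameters will be within the desired range if patient adherence is improved".

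Study strengths & limitations admits that GMAS may overestimate adherence and answers: "However, patient clinical outcomes will be monitored to estimate an overall medication adherence rate". It then concedes that under- or overestimation remains possible.

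On the medication review, recorded problems go to the physician, and "The changes done by the physician will be notified to the researcher and can be tracked in the following follow up". Patient selection states that drug name, dose, frequency, route and duration are taken from the health records. The Statistical analysis section names a correlation of adherence with quality of life only.

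**The concern.** A laboratory value can inform on adherence only if the patient has been prescribed something to take for it. GMAS is a total over all of a patient's medicines, so a patient without a glucose-lowering drug still supplies a GMAS score and a glucose value. That pair carries no information on whether glucose-lowering treatment is taken. The same holds for LDL without lipid-lowering treatment, and for any other parameter in a patient with no drug for it.

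The medication review is a second difficulty. It is part of the intervention and is meant to prompt changes to prescriptions. A value that moves because a prescription changed would, under the surrogate wording, be read as a sign of better or worse adherence.

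At stake is the meaning of the one counterweight that the article offers to self-report bias. A weak link between laboratory values and GMAS could mean that GMAS is inflated, or only that many patients were not on a relevant drug. A laboratory improvement could come from adherence or from prescribing.

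**Working it through.** **The plan's own figure.** The only calculation in the article is the sample size, with δ = 0.9, σ = 1.84, two-sided α = 0.05 and power 0.95. The normal formula gives ((1.960 + 1.645) × 1.84 / 0.9)² = 54.3, rounded up to 55. With the paired t-test, power at 56 pairs is 0.949 and 57 pairs are needed to reach 0.95. The stated 56 is therefore reproduced. It is not presented as a laboratory figure and does not settle this point.

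**Inputs for the correlation**
- Treated share p for a parameter: not in the documents. Assumed range 0.25 to 1. It will differ between parameters.
- Correlation r between laboratory value and GMAS in treated patients: not in the documents. Assumed 0.3 or 0.5.
- In patients without a drug for the parameter: correlation 0.
- Both measures are assumed to have the same mean and variance in treated and untreated patients.

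**Attenuation.** The pooled covariance is p × r × SD(lab) × SD(GMAS) + (1 − p) × 0. Dividing by the two standard deviations gives a pooled correlation of p × r.

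| p | r = 0.3 | r = 0.5 |
|---|---|---|
| 1 | 0.300 | 0.500 |
| 0.9 | 0.270 | 0.450 |
| 0.75 | 0.225 | 0.375 |
| 0.5 | 0.150 | 0.250 |
| 0.25 | 0.075 | 0.125 |

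A pooled 0.25 is what r = 0.5 with half the patients treated would give (0.5 × 0.5). It is also what r = 0.25 with all treated would give (1 × 0.25). The pooled result cannot separate the two. If mean levels also differ between treated and untreated patients, a between-group component is added and can act in either direction.

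**Does restriction lose more than it gains?** Take Fisher's transformation, ½ ln((1 + r)/(1 − r)) × √(n − 3), as an approximate signal-to-noise ratio with 56 completers and r = 0.5 in treated patients.
- p = 0.5. All 56 patients, correlation 0.25: 0.255 × √53 = 1.86. The 28 treated, correlation 0.50: 0.549 × √25 = 2.75.
- p = 0.9. All 56 patients, correlation 0.45: 0.485 × √53 = 3.53. The 50 treated, correlation 0.50: 0.549 × √47 = 3.77.

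Under this model the restricted analysis is the more informative despite the smaller n. The gain is small where nearly everyone is treated.

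**Prescription changes.** This break does not depend on p and remains at p = 1. Study procedure and follow up has the review at the first visit and the outcome assessment at 12 months, so changes that follow the review fall between the two laboratory measurements. The article gives no rate of such changes, so their effect cannot be sized.

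**The case against.** Several counter-arguments are sound.

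- The laboratory values are also clinical outcomes in their own right. The abstract and the introduction ask whether the package improves clinical outcomes in dialysis patients. For that question the whole-cohort change is the natural estimate.
- A reader might infer that this whole-cohort test is itself diluted. Borrowing the plan's 0.9/1.84 as the effect in treated patients, with zero in the rest, gives power at n = 56 of 0.42 against 0.70 in treated patients only when p = 0.5, and 0.89 against 0.92 when p = 0.9. The documents do not support that reading. They give neither p nor a laboratory effect, and a patient untreated at baseline may be started on treatment after the review, so zero effect does not follow.
- The correlation is offered as something that can be done and is not named under Statistical analysis. Details of its analysis set may stand in a full protocol or analysis plan that is not shown. Study strengths & limitations mentions no correlation and admits that misestimation remains.
- The introduction describes multiple comorbidities and frequent polypharmacy in these patients, so p may be high for some parameters.

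These arguments limit the point but do not remove it. The surrogate claim is stated without qualification for an unselected cohort, and nothing shown ties a parameter to patients who take a drug for it.

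**Conclusion.** The point holds for the adherence reading only, and it is modest because it touches a secondary analysis. Patients with no drug for a parameter attenuate the correlation with GMAS to about p × r, under the assumptions of no correlation in those patients and equal means and variances. The loss is half at p = 0.5 and a tenth at p = 0.9; the actual share is unknown. Prescription changes after the review confound the reading at any p, by an amount that cannot be sized from the documents.

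A reader might go further and call the link between laboratory values and adherence invalid. That is right for an individual patient with no relevant drug. For the pooled cohort the link is attenuated and confounded, and it is not shown to be absent.

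**What to change.** 1. Keep the whole-cohort pre-post change in each parameter as the tested clinical outcome of medication review plus motivational interviewing.
2. For the surrogate reading and the GMAS correlation only, analyse each parameter in patients prescribed at baseline at least one drug for it that they take themselves. Report the number of patients for each parameter.
3. Beside each result, report how many of these patients had the relevant prescription changed after the review. Repeat the analysis in those with an unchanged regimen as a sensitivity analysis only, because that group is selected on an event after the intervention began and the selection can itself bias the result.
4. Reword the surrogate sentence under Secondary outcomes and the sentence on the overall adherence rate under Study strengths & limitations, so that an all-patient laboratory change is attributed to the package and not to adherence.

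The cost is in wording and analysis sets. The drug data are already collected under Patient selection, and the medication review already tracks changes. The downside is fewer patients in the correlation analyses: with 56 completers, 42 at p = 0.75 and 28 at p = 0.5.

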### Interventions

Two interventions will be provided in this study: medication review and motivational interviewing.

#### a) Medication review

MR is a well-structured method to optimize medication use and improve health outcomes among patients [31]. The researcher will examine patient medical records and interview patients to identify patient medication discrepancies and medication-related problems. Any medication issue related to a patient’s medicine-taking behavior and use of medicine in the context of their clinical condition will be recorded. The PCNE version 9 and kidney-related clinical practice guidelines will be used as guides. All the recorded medication problems will be discussed with relevant physician. The changes done by the physician will be notified to the researcher and can be tracked in the following follow up.

#### b) Motivational interviewing

Motivational interviewing is an interactive counseling style in which patients are engaged in the process of thinking and talking about their medication-taking behavior. This novel intervention will be used to empower patients with necessary information about their diseases, to address their beliefs around medication, to overcome barriers for nonadherence as well as to provide specific instruction to optimize the use of each medication on an individual basis [32, 33]. This technique emerged from previous alcohol and drug treatment literature, and the efficacy is supported by scientific evidence for the management of substance abuse and other chronic illnesses [34, 35]. This approach consists of the aforementioned four domains that will be used in this study: providing information about diseases, addressing beliefs on medication, overcoming barriers for nonadherence, and providing specific instructions to optimize the use of each medication. These domains are aligned to the MI principles and strategies described by Miller & Rollnick [19]. Before the initiation of the study, the researcher will receive training regarding MI techniques from a professional counselor. Training for MI skills consists of reading materials, viewing video demonstrations related to MI, and attending training with the counselor. Through this, the pharmacist will be equipped with essential skills to engage with the patients. The MI technique in this study will be carried out without a structured guideline to ensure the flow of the sessions, as studies have indicated the traditional method may produce poorer outcomes [36]. In addition, patients will be given knowledge alone is not sufficient regarding their medication, disease management, targeted clinical parameters and side effects of medication.

### Study procedure and follow up

Once informed consent is obtained from the eligible patients at the first month’s visit, patients’ medication adherence, QOL and lab results—mainly the calcium, phosphate, hemoglobin, lipid profile, and glycosylated hemoglobin levels will be assessed. A medication review will also be performed. The updated list and observations/recommendations will be provided to the physician in charge. The medical records will be reviewed in the following six months to determine whether individual discrepancies have been corrected and whether MRP recommendations have been accepted by the prescriber. Motivational interviewing will be conducted in 3 sessions, in the 3^rd^, 6^th^ and 9^th^ months. Each session will last approximately 15 to 20 minutes for each patient. Only the first session will be done face to face (during the patient’s scheduled dialysis day) to build a good relationship with the patient, while the second and third sessions will be conducted over the phone to minimize close contact with the patients during the COVID-19 outbreak period. This method has proven its efficacy in previous research [37] and ensures safety for both patients and the researcher. The number of sessions to motivate and improve medication adherence has been set at three, as the optimal number is not known [38–40]. At the final visit (12 months), the medication review will be performed, medication adherence, QOL score and lab parameters will be assessed. The pre-post results will be checked for significance in improvement using the software package Statistical Package for Social Sciences (SPSS) Version 26.0. The results will be evaluated to check if there are any significant changes in the number of medication-related problems, adherence and QOL at the end of patient-centered pharmacist care. The summary of study procedure is shown in Fig 1.

**Fig 1 pone.0263412.g001:**
[figure not shown]
Flow chart summary of study procedure.

All the recruited patients only can do their hemodialysis in the registered respective HD unit. They must strictly follow to their HD schedule, check blood sample every 3 months and reviewed by the nephrologist. This is the practice in the HD unit (at the study site) included. Patients’ movement control can be easily monitored, and the lab results will be captured in their medical records appropriately. Hence, missing data is avoided. As the interventions done every 3 months, the researcher can get the sufficient information from the patients and medical records. Patient missed appointments due to logistic reasons will be rescheduled within one week interval. However, missed appointment for more than 3 times due to hospitalization or changes in disease state, the case will be discussed with physician and co-researchers. Based on the expert opinion, decision on exclusion of the patient will be made.

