#### Statistical analysis

Continuous variables will be expressed as mean ± standard deviation or median and interquartile range. Categorical variables will be expressed as a percentage. Adherence and QOL patterns before and after intervention will be assessed using paired sample t-tests or Wilcoxon signed-rank tests, depending on the sample distribution. Pearson correlation coefficient or Spearman rank correlation coefficient tests will be used to evaluate the associations between adherence and QOL. A general linear model will be applied to find the factors associated with MRPs, adherence and QOL. Data will be analyzed using SPSS Version 26.0. The significant level will be set at p < 0.05.

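### Excluding enrolled patients on expert opinion after repeated health-related absence, without criteria, risks selective loss in a single-group pre-post study

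*Protocol article*

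**What the plan says.** All of this is in the protocol article.

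- **Study procedure and follow up, text after Fig 1.** Absence is handled by cause. For logistic misses: "Patient missed appointments due to logistic reasons will be rescheduled within one week interval". For "missed appointment for more than 3 times due to hospitalization or changes in disease state", the route is different: "the case will be discussed with physician and co-researchers", and then "Based on the expert opinion, decision on exclusion of the patient will be made". The text gives no criteria for that decision and does not say whether an excluded patient's data stay in the analysis.
- **Same paragraph.** After describing the fixed dialysis schedule, the three-monthly blood tests and the capture of laboratory results in the records, it concludes: "Hence, missing data is avoided".
- **Study procedure and follow up.** "Motivational interviewing will be conducted in 3 sessions, in the 3^rd^, 6^th^ and 9^th^ months". The final assessment is at 12 months.
- **Statistical analysis.** Adherence and quality of life before and after the intervention "will be assessed using paired sample t-tests or Wilcoxon signed-rank tests, depending on the sample distribution".
- **Study design.** 56 pairs are required. Fourteen patients are added for a 25% dropout rate, giving 70.
- **Study strengths & limitations.** The 25% may be too low: "As ESRD patients are high risk patients with high mortality and morbidity rates".

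**The concern.** The rule selects on health. A patient absent for practical reasons is brought back. A patient absent because of hospital admission or a change in disease state can be removed, by people who may know how that patient is doing.

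The within-patient change is the whole effect estimate here, and no control group shares the selection. If those removed would have changed less well than those kept, the result describes patients who stayed well enough to attend, yet it would be read as the effect of the programme in haemodialysis patients generally. The dropout allowance does not help: extra patients restore precision but leave selection bias where it is.

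**Working it through.** **1. The plan's own figure.** Inputs from Study design: difference 0.9, SD of paired differences 1.84, two-sided alpha 0.05, power 0.95.

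- Normal formula: n = ((1.96 + 1.645) × 1.84 / 0.9)² = 54.3, so 55 pairs.
- Exact t calculation: 57 pairs; at 56 the power is 94.9%.

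The stated 56 is reproduced to within two patients. The total is 56 × 1.25 = 70. The protocol therefore supports two loss figures: the 14 patients added, or 25% of 70 = 17.5, about 18.

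**2. How selective loss enters the estimate.** Let f be the share lost.

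Bias of the completer mean = f × (mean change in retained − mean change in lost).

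The bias is zero if the two groups change equally, whatever their levels. The documents give neither f for this rule nor the difference in change, so the bias cannot be computed from them.

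**3. Illustration at the planned loss rate.** Assumptions: all planned loss is of this kind, completers improve by 0.9, and lost patients do not change.

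| Lost of 70 | Mean over all enrolled | Completer estimate / all-enrolled mean |
|---|---|---|
| 14 | 0.9 × 56/70 = 0.72 | 0.9/0.72 = 1.25 |
| 18 | 0.9 × 52/70 = 0.67 | 0.9/0.67 = 1.35 |

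The ratio is simply 70 divided by the number retained, so it does not depend on the 0.9.

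**4. Wider range.** Here the change in lost patients is assumed to be worse by g SDs (SD 1.84), so bias = f × g × 1.84. The last column is the chance that the two-sided 5% test in those retained rejects when the true mean change over all patients is zero.

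| f | g | Bias | Share of 0.9 | Rejection |
|---|---|---|---|---|
| any | 0 | 0 | 0% | 5% |
| 5% | 0.5 | 0.05 | 5% | 5.5% |
| 10% | 0.5 | 0.09 | 10% | 6.8% |
| 10% | 1 | 0.18 | 20% | 12% |
| 25% | 0.5 | 0.23 | 26% | 14% |
| 25% | 1 | 0.46 | 51% | 42% |

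**5. What counts as an appointment.** The word is undefined, and the reach of the rule depends on it.

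- *Study contacts.* After baseline there are four: months 3, 6, 9 and 12. More than three missed means all four, so the patient already has no month-12 questionnaires and drops out of a paired test with or without formal exclusion.
- *Dialysis or clinic visits included.* Participants dialyse three times a week, so four missed sessions span 4/3 weeks, little more than one week. A patient whose month-12 data could still be obtained might then be removed.

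**6. The missing-data statement.** Its argument concerns laboratory results held in records. It does not cover GMAS or KDQOL-36, which need the patient to answer. It also cannot stand as a general statement beside a 25% allowance made partly for incomplete data and a limitation warning that this may be too little.

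**The case against.** The strongest reply is that the rule is narrow. It needs more than three misses with a health-related cause, and then leads only to a discussion; exclusion is possible, not automatic. If appointments are the study contacts, it adds almost nothing to ordinary dropout for adherence and quality of life. That stands for that reading. It does not settle the other reading, nor outcomes that can be traced in records (laboratory values and, in part, medication-related problems, the primary outcome).

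A reader might infer that the rule removes the sickest patients and biases the change upward. The documents do not support that:

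- They speak of changes in disease state, not worsening.
- Bias needs the change, not the level, to differ. Sicker patients may start with more problems and have more room to improve. A favourable bias is plausible but not shown.
- *Upward* is the wrong sign for the primary outcome, where fewer problems is better.

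A reader might also put the overstatement at about twofold: with 18 lost who each worsen by 0.9, the all-enrolled mean is (0.9 × 52 − 0.9 × 18)/70 = 0.44. Nothing in the protocol supports that assumed worsening, and the dropout allowance covers loss for any reason, not this rule alone.

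Finally, the analysis set may be defined in a document not shown, so a completer-only analysis is an inference from the paired tests, not a stated choice. The authors also disclose the mortality risk. Both points are fair. Neither removes an exclusion rule that the article itself states.

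**Conclusion.** The point holds as a risk created by a stated rule. Exclusion after enrolment is discretionary, has no criteria and is open only to patients with health-related absence. With no control group and paired tests, it may make the change look more favourable. Its direction is likely rather than proven, and its size is unknown. The 25% to 35% figures are illustrations that assign all planned loss to this mechanism and assume no change in those lost; at 5% to 10% loss and a half-SD difference, the bias is 5% to 10% of the planned 0.9. Two wording faults stand without any assumption: *appointment* is undefined, and the missing-data statement is broader than its argument and at odds with the dropout allowance.

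**What to change.** 1. Replace the exclusion sentence with: *No consented patient is excluded from follow-up or analysis because of missed appointments; month-12 medication review, questionnaires and labs are still sought, at a dialysis session where possible.*
2. Report reasons for loss, with baseline values of completers and non-completers side by side.
3. Add a sensitivity analysis that sets patients without month-12 data to no improvement.
4. Delete the statement that missing data is avoided, or limit it to laboratory values.

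A mixed model is optional. It would help mainly the laboratory values, which have a month-6 measurement. Medication review, adherence and quality of life are scheduled only at baseline and month 12, so it adds little there, and it would rest on a missing-at-random assumption that is in doubt here.

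The cost is wording and a little more analysis. The estimated change may be smaller.
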